### Design

This is a hybrid type 2 cluster randomized feasibility trial, with 16 health facilities in Malawi assigned to either a clinic-only or a clinic-and-community model for CCSPT. The study will take place over a period of 2.5 years, with a pre-implementation phase of 6 months, an implementation phase of 18 months, and a dissemination phase of 6 months (Fig. 1 and Table 1).

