**Table 1 Tab1:**
[figure not shown]
Work plan

The pre-implementation period will be used for obtaining ethical approvals, developing study-specific forms and procedures, selecting and randomizing facilities, and preparing facilities to offer the new services through equipment procurement, facility rehabilitation, and training. We will also complete time-and-motion evaluations and the first round of mixed methods assessments, involving interviews, focus groups, and surveys, to understand the baseline situation. During the implementation period, we will perform additional rounds of mixed methods assessments and collect routine service utilization data from each facility. Assessment details are provided in Table 2. Near the end of the implementation period, we will conduct an Endline Household Survey to assess uptake of CCSPT and FP services among women who live in the catchment areas of the health facilities. The Endline Household Survey will allow us to compare the screening and treatment rates of the clinic-only and the clinic-and-community model.

**Table 2 Tab2:** Descriptions of assessments, organized by objective

Assessment	Description	Participants	Sample size
Objective 1: Compare the proportion of eligible women who receive CCSPT and FP services in the catchment areas of health facilities assigned to the two models.			
Endline Household Survey	The survey covers prior and recent use of CCSPT and FP services.	Women residing in the catchment areas for the health facilities; must be aged 15–50 years and cannot have had their cervix removed.	8000 women
Objective 2: Assess the acceptability, appropriateness, and feasibility of the two models among key stakeholders, including providers, facility management teams, and clients			
Baseline Assessment Form	The form collects information about the facility’s capabilities for providing CCSPT and FP services.	Completed by research assistants, one form per facility	16 forms (one per facility)
Readiness Assessment Forms	The form includes Likert scale rankings for various parameters of the readiness of the facilities/health system to implement the two models. Participants will answer the survey in small groups, coming to consensus on each ranking.	District health management team members, health facility managers, and community stakeholders	16 forms (one per facility)

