Service utilization data	De-identified information about CCSPT and FP services will be collected from clinic, HSA, and lab registers on a monthly basis.	Providers routinely record visit information in registers; research team members collect data	N/A (difficult to estimate projected number of clients for each register type)
Time and motion study	Research assistants will continuously observe providers, e.g., nurses and HSAs record the time spent on health care activities such as CCSPT and FP including non-health care activities	Providers, nurses, clinicians, HSAs, and lab staff	At least 1 staff member per facility from each category (e.g. provider, HSA, lab staff).
Client Exit Survey	This survey asks clients about the money and time expended accessing CCSPT and FP services at the clinics. It also includes the EQ-5D-3L survey to assess health-related quality-of-life for the cost impact analyses.	Facility clients	Up to 2370 participants (790 participants each at 3 time points, with the number of participants interviewed per facility proportional to the number of FP clients at that facility)

Throughout the implementation period, we will conduct weekly clinical supportive supervision visits and mentor the health facility providers, ensure appropriate logistical support, and assess providers’ fidelity to our protocols. Of note, while our study is ongoing, we will not restrict concomitant care or interventions at the study sites. Specifically, facilities are permitted to continue offering VIA and cryotherapy.

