#### Endline Household Survey

The Endline Household Survey, conducted at months 13–15 after implementation, will be the primary tool to assess the uptake of CCSPT and FP services among women in the catchment areas of the health facilities. Households will be sampled in a two-stage sampling design. Stage 1 will include a random sample of enumeration areas (EAs) from all of the facilities’ catchment areas. This random sample will be selected with the number of EAs proportional to the size of the catchment area. In each selected EA, we will undertake a household listing to create a sampling frame of households for the survey. In stage 2, a random sample of households will be selected. Our target sample size is up to 8000 women aged 15–50 years from the 16 health facility catchment areas. The age range is intended to include women most likely to utilize FP services, as well as those in the target range for CCSPT. With the expectation of ~1.1 women aged 15–50 in our households, the sample will include ~8000 households selected from 266 EAs selected proportionally from facility catchment areas (randomly selecting ~30 households/EA). Parental consent will be obtained for participants 15–17 years old, as described in the “Ethical considerations” section. If a randomly sampled woman does not consent for the survey, she will be replaced with another randomly selected woman from her EA.

Women aged 15–50 years will be eligible to participate in the interviewer-administered survey, provided that they have not had their cervix removed. The survey will cover demographic information, reproductive health information, HIV status, distance to the nearest health facility, prior FP use, FP use during project implementation, prior CCSPT services received, and CCSPT services received during project implementation.

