### Analysis plan

#### Endline Household Survey

Key outcomes from the Endline Household Survey include (1) the proportion of eligible women who have received CCS during the 18 months of study implementation, (2) the proportion of treatment-eligible women who received thermal ablation during the study period, and (3) the proportion of women aged 15–50 years who are using a modern FP method. These proportions will be calculated using descriptive statistics. Differences between the clinic-only and clinic-and-community models will be assessed via logistic regression, adjusted for district, facility size, and facility type. The regression model will account for health facility clustering, and analyses will be adjusted for the small number of clusters [28, 29].

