#### Cost and budget impact

For the CCSPT intervention proposed, we will calculate the incremental cost of the two models (including both costs incurred and averted), the cost per woman screened, and the cost per cervical cancer case averted. We will also estimate the cost per use of CCSPT and FP services. Cost data will be used to conduct a budget impact analysis from the Malawi MoH perspective.

Micro-costing studies will use the time and motion evaluations, routine service utilization data, study budgets, workload assessments, structured observations, and client exit surveys. Estimated costs will also be abstracted from published government reports and the health economics literature, based on methods from published cost-effectiveness research [31, 32]. Costs will be compared between the two models and between each model and the current standard of care (VIA and cryotherapy). The number of women screened will be based on the results of the Endline Household Survey.

To estimate the impact of HPV screening and treatment, we will use a decision analysis model to simulate HPV infection, clearance, persistence, and progression to high-grade cervical intraepithelial lesion and cancer (CIN2+), informed by previous modeling work [33, 34]. Our modeling will also capture differences in cost and outcomes by HIV status.

For budget impact analysis, we will consider direct program costs, to ensure that measurements of MoH costs reflect the opportunity cost of the resources used in delivering services. The primary analysis will be from the programmatic perspective, the point of view of decision makers. A secondary analysis will be presented from the societal perspective, using data on economic productivity for disease averted and costs of accessing services.

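### Cost per woman screened takes its count from a resident survey at months 13–15, while costs are not cut off before month 18; the two should cover the same months and people

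*Protocol article*

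**What the plan says.** The analysis plan for cost and budget impact names "the cost per woman screened, and the cost per cervical cancer case averted" among its results. For the count it states: "The number of women screened will be based on the results of the Endline Household Survey".

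The survey's timing is given under Assessments: "The Endline Household Survey, conducted at months 13–15 after implementation". The Design section describes "an implementation phase of 18 months", and the text accompanying the work plan confirms that the survey falls inside that phase: "Near the end of the implementation period, we will conduct an Endline Household Survey". Table 2 restricts survey participants to women living in the facility catchment areas.

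The third objective draws costs from expenditure during implementation, without giving months. For the same objective, Table 2 lists a second source of counts: "De-identified information about CCSPT and FP services will be collected from clinic, HSA, and lab registers on a monthly basis". The cost section uses routine utilization data for micro-costing but does not name it as the source for the number of women screened.

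**The concern.** A unit cost is interpretable only if the money and the women it served are counted over the same period and the same clients. Two mismatches arise here.

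- **Time.** A woman interviewed in months 13–15 cannot report a screen that happens later, yet that screen uses cartridges, staff time and supervision.
- **People.** The clinic eligibility criteria under Description of models contain no residence requirement, so women from outside the catchment can be screened and cost money without being in the survey population. Community sampling in model 2, by contrast, is offered to catchment residents.

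In addition, the survey gives a self-reported proportion from a sample, which must be scaled to a number of women.

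At stake is a named result of the third objective, intended for Ministry of Health decision makers, and possibly the hypothesis that model 1 is more cost-effective than model 2. The primary outcome is not affected by this choice.

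**Working it through.** The protocol gives no unit cost and no count of women screened, so there is no figure to reproduce. The check is a ratio.

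**Inputs from the protocol.** Implementation lasts 18 months (Design). The survey month S is 13 to 15 (Assessments). The survey covers catchment residents (Table 2). VIA may continue at the sites (text after Table 2).

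**Assumptions.** Costs cover all 18 months. The share of 18-month screens that have happened by month S is (S/18)^g, where g = 1 is uniform accrual, g = 0.5 front-loaded and g = 2 back-loaded.

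**Step 1: timing alone.** Factor on cost per woman screened = 1 ÷ share seen = (18/S)^g.

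| Survey month | Share seen, g = 1 | Factor, g = 1 | Factor, g = 0.5 | Factor, g = 2 |
|---|---|---|---|---|
| 13 | 13/18 = 72% | 1.38 | 1.18 | 1.92 |
| 14 | 14/18 = 78% | 1.29 | 1.13 | 1.65 |
| 15 | 15/18 = 83% | 1.20 | 1.10 | 1.44 |

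If costs are cut at the survey month, the factor is 1.00.

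**Step 2: costs built up per screen.** Suppose only a fraction f of the true unit cost is a shared total divided by the count, and the rest is a per-screen input. The factor is then 1 + f × (18/S − 1). With f = 0.5 as an illustration, it is 1 + 0.5 × 0.20 = 1.10 at month 15 and 1 + 0.5 × 0.385 = 1.19 at month 13. The protocol does not give f.

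**Step 3: other errors in the survey count (month 14, uniform accrual).** Let o be the share of programme clients who live outside the catchments, and e the relative excess from screens the programme did not fund or from over-reporting. Factor = 1 ÷ [(14/18)(1 − o)(1 + e)].

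- o = 10%, e = 0: 1.43; o = 20%, e = 0: 1.61.
- o = 0, e = 20%: 1.07; e = 30%: 0.99; e = 40%: 0.92.
- With o = 0, the timing effect is cancelled when e = 18/S − 1, which is 20% at month 15 and 38% at month 13.

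The values of o and e are assumed ranges; the protocol gives neither.

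**Step 4: model 2 against model 1 (month 14).** The ratio of unit costs is multiplied by (18/14)^(g₂ − g₁). With the same accrual shape in both models this is 1.00. With one model at g = 1 and the other at 0.5, 1.5 or 2, it lies between 0.78 and 1.29, and either model can be favoured.

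**The case against.** The strongest reply is that the cost window is not stated in months. Costs might be stopped at the survey date, and a journal article can leave that detail to the full protocol; the timing factor would then be 1.00. This stands as a limit on the size of the problem. It does not remove it, because the source of the count is fixed in the text and the people mismatch remains whatever the window.

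Second, the planned micro-costing draws on time-and-motion and utilization data, so part of the cost may be assembled per screen and would not inflate. This also stands, and Step 2 shows its effect.

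Third, a survey count has merits. It counts women rather than visits, it matches the trial's primary effectiveness measure, and coverage is a natural input to the decision model. These are good reasons to keep it for coverage, but not to divide programme expenditure by it.

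Three stronger readings are tempting, and the protocol does not support them:

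- **Unit cost will certainly be overstated.** VIA may continue at the sites, the survey outcome is screening in general, and self-report can run high. Each enlarges the count and could cancel or reverse the timing effect.
- **The registers capture every screen.** Table 2 describes de-identified visit information, and completeness is not stated. Double data entry limits transcription error, not missing or repeated entries.
- **The budget impact inherits the error.** That analysis is described as resting on direct programme costs; nothing says it is built on cost per woman screened.

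**Conclusion.** The concern holds in a limited form. The plan takes its count from a survey of residents that ends three to five months before implementation does, and nothing aligns the costs with it. Timing alone would overstate cost per woman screened by about 20–38%, provided that costs cover all 18 months, accrual is uniform and the cost is a total divided by the count. Under the front-loaded pattern it is 10–18%, and it shrinks further where costs are built per screen.

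The net direction is not established, because non-resident clients add to the overstatement while unfunded or over-reported screens reduce it. Offsetting errors of unknown size are no defence of the figure. Distortion between models is conditional on accrual, non-resident use or reporting differing by model, and the protocol has no figure showing that they do.

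A related inconsistency adds to the doubt about the window. The analysis plan defines the survey outcome as "the proportion of eligible women who have received CCS during the 18 months of study implementation", which a survey at months 13–15 cannot observe in full, and the hypotheses under Aims and objectives speak of 12 months. If a 12-month count met 18-month costs, the uniform-accrual factor would be 18/12 = 1.50.

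**What to change.** In the cost and budget impact section of the analysis plan:

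1. State the months and facilities over which costs are counted.
2. Take the primary count for cost per woman screened from the clinic, HSA and laboratory registers for those same facilities and months, with a stated rule for repeat screens.
3. Keep the survey for population coverage. Present a survey-based unit cost only as a sensitivity analysis, with costs cut at the survey date.
4. Reconcile the 12-month, 18-month and month 13–15 statements.

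The cost is wording only. Register data are already to be collected monthly and double entered, and new laboratory and community-screening registers are planned under Facility preparation. The downside is that registers are de-identified visit records, so repeat screens and incomplete entries may leave some error; the report should say so.

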### Ethical considerations

This study has been approved by the University of North Carolina Institutional Review Board (IRB#: 19-0638) and the National Health Sciences Research Committee of Malawi (NHSRC#: 19/03/2255). All protocol modifications will be communicated to these regulatory boards, and protocol modifications relevant to health care provision will be communicated to study sites. The currently approved version of the protocol is Version 2.0, dated September 6, 2019, and is the version presented here.

Written informed consent will be obtained for participants in the Endline Household Survey, IDIs, and FGDs. This will include women living in the catchment areas of the facilities who are randomly sampled for the Endline Household Survey, facility managers, providers, and HSAs, and a small selection of CCSPT clients. Adolescents may be sampled for Endline Household Survey because women aged 15–50 years are eligible. For any potential participants aged 15–17 years, we will require both pediatric assent and parental consent for enrollment. IDI/FGD sessions will be conducted by experienced qualitative researchers, who are accustomed to leading sensitive discussions.

Research participants will be identified only by a unique study identification code on all records. We expect that any adverse events related to study participation will be social harms, and we do not anticipate any serious adverse events. Any study site staff member or research team member can report protocol deviations or social harms to the study coordinator who will record them in the *Protocol Deviations and Social Harms Log*, which will be submitted to the IRBs on an annual basis. Because risks to participants are minimal, a data and safety monitoring board will not be required for this study.

The requirement for informed consent was waived by the ethical committees for all assessments besides those listed above as they do not involve collection of identifiable data. All data is securely stored on the UNC OneDrive on the UNC server, and only research staff who have received ethical committee approval have access to it through their private email address and password. Data collected from the registers is double entered into the database to minimize data entry errors. The final trial datasets will be uploaded to USAID’s Development Data Library for open access.

## Discussion

Malawi has struggled to achieve widespread CCSPT coverage and carries a disproportionate burden of cervical cancer. Given recent advances in technology, including the Xpert HPV assay, HPV-based screening programs are more feasible to implement in resource-limited settings, and the stability of self-collected cervicovaginal samples opens up the opportunity for community-based screening. Meanwhile, thermal ablation provides a less resource-intensive alternative to cryotherapy for treatment. Our cluster randomized trial will provide key insights into the effectiveness, acceptability, appropriateness, feasibility, and budget impact of clinic-only and community-and-clinic models for implementing HPV-based screening in Malawi. We expect the clinic-and-community model to be more effective, acceptable, and appropriate. Community-based services may be more difficult and expensive to implement than clinic-only services, but we hypothesize that community screening will still be feasible in Malawi and more cost-effective than the current standard-of-care. Community programs also uniquely hold the potential to reduce disparities in screening and improve health equity.

Studies in other low-resource countries have demonstrated that training community health workers like HSAs to offer self-sampling is feasible and has the potential to improve screening coverage. In addition, the WHO now recommends self-testing options for sexual and reproductive health, including HPV self-sampling for primary cervical cancer screening [4]. A cluster randomized study in Argentina demonstrated a four-fold increase in screening rates with community health workers offering HPV self-sampling, compared with community health workers counseling women to undergo clinician-sampling at a facility [18]. In Uganda, screening was higher with community-based HPV self-sampling compared to the control of clinic-based VIA screening, in preliminary results from a cluster randomized trial [19]. The same project showed that community-based HPV self-sampling was more cost-effective than clinic-based VIA screening, with a wide margin for increasing costs of the HPV-based program [35]. Our study will investigate the feasibility of community self-sampling in Malawi and provide a direct comparison to facility-only services. Using stratified randomization further allows us to assess implementation success in a variety of settings, including urban and rural, district-level and local, and public and private facilities.

Linking community-screened women with appropriate care is crucial for cervical cancer prevention and can be especially challenging with community-based screening. In the pilot results of a Uganda trial comparing community HPV screening versus clinic-based VIA screening, over 50% of 73 women who were positive for hrHPV after community self-sampling could not be reached by telephone for result delivery [19]. Loss to follow-up is already a concern with the current standard of care in Malawi: only 43% of women who are VIA-positive receive appropriate treatment [3]. Our study will provide insight into whether appropriate follow-up is feasible with community-based screening.

Studies never perfectly approximate real-world settings, but we have tried to increase fidelity by working closely with facilities and MoH partners to ensure that we are implementing only interventions that could be realistically maintained by these partners after the study period. This approach could potentially become challenging as there could be expectation from providers for incentives, which if implemented would make our study vulnerable to unrealistic conclusions about the feasibility of our interventions.

Disseminating findings to local partners is a priority for our team, since we hope that our study results will directly inform policy in Malawi. Key stakeholders, including the MoH, will already be engaged with our project by serving on our project’s advisory board and attending our regular stakeholder meetings which are intended primarily to validate our findings and seek explanations for successes and failures. After project completion, we plan to hold a large dissemination meeting with relevant policy makers, academic institution representatives, and private health leaders. To contribute to the larger body of evidence on context-appropriate CCSPT solutions, we will present our findings through peer-reviewed journals and regional and international conferences as per the CONSORT 2010 statement for randomized pilot and feasibility trials [36]. We will also present our findings to the MoH committees involved in family planning and CCSPT services. Progression of implementation of our interventions will depend on the input and agreement of our key stakeholders, including these MoH committees, as well as the availability of funding to pay for HPV cartridges once funding for our trial ends.

In accordance with USAID’s Operational Policy Automated Directives System Series 500, Chapter 579, and the newly approved Public Access Plan, the research team will submit the study dataset using the platform-independent and non-proprietary comma-separated values (also known as [CSV]) format. The study dataset will be submitted to USAID’s Data Development Library within 30 calendar days after the dataset is first used to produce an intellectual work. For the purpose of this project, “Intellectual Work” is defined as the initial online or print publication of the primary study manuscript. If 30 days is not feasible, the research team will consult with the USAID Agreement Officer Representative to determine a suitable time frame for dataset submission.

